#### Body Composition and Bone Mineral Density

Body composition (whole-body fat mass and fat-free mass) and whole-body areal bone mineral density will be measured at weeks 6 and 24 using a whole-body dual-energy x-ray absorptiometry scan (Lunar iDXA, GE Healthcare). Participants will be scanned in minimal clothing and instructed to lie as still as possible for the approximately 7-minute scan. Participants will arrive at the laboratory in a rested state, at least 3 hours in the postprandial state, and euhydrated, having consumed 500 mL of water in the 2 hours before scanning [47].

#### Bone Density and Morphology

A 3D high-resolution peripheral quantitative computed tomography system (XtremeCT II, Scanco Medical AG) will be used to assess volumetric bone mineral density (vBMD), geometry, microarchitecture, and estimated mechanical strength of the nondominant (self-reported) tibia at 6 and 24 weeks post partum. A 3D representation of approximately 10 mm of the tibia in the axial direction, at both the metaphyseal (4% site) and diaphyseal (30% site) tibia, will be obtained from 165 computed tomography slices with an isotropic voxel size of 61 μm. Tibial length will be measured before the first scan, taken as the distance between the medial malleolus and the tibial end plate. The leg of each participant will be fitted into a carbon fiber shell and immobilized within the gantry of the scanner for the duration of the scan. A reference line will be placed at the tibial end plate, with the first computed tomography slice taken at 4% and 30% of the tibial length from the reference line for the metaphyseal and diaphyseal tibia. For follow-up measurements at the 4% site, automatic algorithms will match the volumes of interest to baseline scans, using the cross-sectional area (CSA) within the periosteal boundary, so only the bone volume common to the baseline scans will be assessed [48]. The matching algorithms will be disabled for analysis at the 30% site [49]. Daily quality control scans will be performed using a phantom containing hydroxyapatite (HA) rods. The quality of each high-resolution peripheral quantitative computed tomography scan will be reviewed according to the manufacturer’s visual grading system, and poor-quality scans will be excluded. Data processing will be performed as per Boutroy et al [48] and Burghardt et al [50]. The manufacturer’s standard evaluation procedure will be used to derive the following outcomes: total vBMD (mg HA∙cm^3^), trabecular vBMD (mg HA∙cm^3^), cortical vBMD (mg HA∙cm^3^), trabecular bone volume fraction (%), trabecular area (mm^2^), cortical area (mm^2^), cortical thickness (mm), trabecular thickness (mm), trabecular number (mm^−1^), trabecular separation (mm), cortical porosity (%), and cortical pore diameter (mm). The biomechanical properties under uniaxial compression, specifically stiffness (kN/mm) and failure load (kN), will be determined by micro–finite element analysis [51]. Evaluations will be performed by the same researcher to ensure consistency of periosteal and endosteal contouring. The coefficient of variation at the 4% site is 0.2% for total vBMD, 0.4% for trabecular vBMD, 0.9% for cortical vBMD, ≤1.3% for geometry, ≤2.1% for trabecular microarchitecture, 7.8% for cortical porosity, and ≤3.2% for stiffness and failure load [52]. The coefficient of variation at the 30% site is 0.3% for total vBMD, 0.2% for cortical vBMD, ≤0.8% for geometry, 4.9% for cortical porosity, and ≤0.7% for stiffness and failure load [52].

#### Patellar Tendon Properties

##### Overview

Measures of patellar tendon biomechanical properties will be obtained in vivo during voluntary isometric ramped contractions [53] at 6, 12, and 24 weeks post partum. All measurements on the dominant limb will be performed by the same researcher.

##### Tendon Elongation

Patellar tendon elongation will be assessed using real-time B-mode ultrasonography during ramped isometric contractions performed at a 90° knee angle on an isokinetic dynamometer (Biodex Isokinetic Dynamometer, System 4). The participants’ dominant leg will be strapped at the ankle to the knee extension and flexion attachment. Straps will be tightly positioned at the shoulder and hip and across the thigh of the leg being measured. Isometric ramped contractions will be performed over 5 seconds. Participants will gradually increase the push against the dynamometer, aiming to reach maximum force within 5 seconds. Each participant will perform 4 preconditioning contractions to ensure reproducibility of the measurements [53] before completing 3 trial attempts. An ecoabsorptive external marker will be fixed to the skin using surgical tape. The ultrasound transducer will be positioned over the patellar tendon and the external marker. Tendon displacement will be measured as the distance between the line cast by the external marker and the patellar apex. Trials will not be analyzed if the line cast by the external marker moves on the ultrasound image. A calibrated goniometer will be attached to the lateral side of the tested knee to prevent an overestimation of tendon elongation due to tibial translation.

##### Surface Electromyography

Surface electromyography (EMG) will be used to measure muscle activity (DataLOG system, MWX8, Biometrics) from the long head of the *m. biceps femoris*. An EMG sensor (SX230, Biometrics) with 20-mm contact sensor spacing will be applied at a site corresponding to the distal one-third of the length of the muscle [53]. The location of the electrode will be traced onto an acetate sheet to ensure its accurate placement for subsequent tests. The raw EMG signal will be preamplified and filtered using high- and low-pass cutoff filters set at 10 and 500 Hz. The root-mean-square EMG activity of the biceps femoris will be measured during ramped contractions to assess the antagonistic coactivation level of the knee flexors. A maximal knee flexion isometric contraction will be performed to determine biceps femoris maximal activation when acting as an agonist. The maximal activation of the bicep femoris will be measured over a 50-millisecond window at the point of the maximum torque. The antagonistic torque of the knee flexors during a knee extension contraction will be calculated assuming a linear relationship between EMG and the torque [54] to calculate the true knee extensor torque.

##### Patellar Tendon Length and CSA

Resting patellar tendon length and patellar tendon CSA will be measured using real-time B-mode ultrasonography at a fixed 90° knee angle. The distance between the apex of the patella and the tibial tuberosity, recorded using sagittal ultrasound images, will be taken as resting patellar tendon length. Patellar tendon CSA will be measured using the ultrasound probe placed in the transverse plane, and images will be captured at 25%, 50%, and 75% of tendon length. Images will be analyzed offline using ImageJ (v1.50c; National Institute of Health), 3 images will be averaged at each site, and the mean will be used for calculating tendon stress.

##### Patellar Tendon Stiffness and Young Modulus

Patellar tendon force will be calculated by dividing the true knee extensor torque by the estimated patellar tendon moment arm [55]. Patellar tendon stress will be calculated by dividing the tendon force by the tendon CSA. Tendon strain will be calculated as the ratio (%) of tendon displacement to the initial resting tendon length. Force-elongation data will be fitted with a second-order polynomial curve, allowing the assessment of patellar tendon stiffness. The Young modulus will be calculated as tendon stiffness multiplied by the ratio of tendon length to tendon CSA.

#### Muscle Architecture

The muscle architecture of the *m. vastus lateralis* will be assessed at 6, 12, and 24 weeks post partum by the acquisition and analysis of B-mode ultrasonography (MyLab Omega, Esaote) images with a 4- to 15-MHz linear array probe, with the participant lying supine. Images of the dominant leg will be taken at 50% of the length of the and at the midsagittal line of the *m. vastus lateralis*. The scan site will be marked and traced onto acetate with reference points for subsequent tests. The transducer will be aligned to the fascicle plane to allow optimal capture of the fascicles [56]. Muscle thickness, fascicle length, and pennation angle will be assessed using digitizing software (ImageJ v1.50c). Muscle thickness will be measured as the distance between the superficial and deep aponeuroses of the *m. vastus lateralis*. Muscle thickness values will be calculated as the mean of measurements taken at the proximal, central, and distal locations on the captured ultrasound image. The visible portion of the fascicle within the scan window will be measured. The nonvisible portion of the fascicle will be estimated by linear extrapolation of the fascicles and aponeuroses. The linear extrapolation method is a valid technique for measuring vastus lateralis fascicle length [57], and to reduce fascicle extrapolation error (reported as approximately 4% [58]), an average of 3 fascicles across the image will be taken. The pennation angle will be determined as the angle created from the visible insertion of the fascicle into the deep aponeurosis. An average of 3 pennation angles will be taken across the image.

#### Muscle Protein and Collagen Turnover

##### Overview

Muscle protein and collagen turnover will be measured between 12 and 18 weeks post partum (Figure 4). Baseline blood and saliva samples will be collected at testing session 2. Participants will then be given a labeled stable isotope tracer (deuterium oxide [D_2_O]) at a dose of 3 mL/kg body weight, divided into 5 smaller doses, and given over 1 hour immediately after the baseline blood and saliva samples are collected. A saliva sample will also be collected 2 to 3 hours after D_2_O ingestion. At testing session 3, a saliva sample and a muscle microbiopsy will be collected.

**Figure 4 figure4:**
[figure not shown]
Procedures for muscle protein and collagen turnover using deuterium oxide (D_2_O).

The blood sample and muscle biopsy will be collected 6 weeks apart. During this 6-week period, participants will take a weekly *top-up* of D_2_O (approximately one-third of the original bolus) at home and will be asked to provide a saliva sample immediately before and 2 to 3 hours after each dose. Because participants will be D_2_O naïve, alanine labeling in plasma proteins reflects the baseline enrichment of body proteins and will be used as a proxy for baseline muscle enrichment. The body water pool will be enriched with D_2_O, and the background enrichment measured from saliva will be compared with the enrichment measured in muscle.

##### Blood Samples

Venous blood will be collected in lithium heparin vacutainers and thereafter centrifuged at 1843 × g and 4 °C for 20 minutes. Plasma will be separated and stored at −80 °C until analysis.

##### Saliva Samples

Saliva will be centrifuged at 4472 × g at 4 °C for 10 minutes to pellet cell debris. The supernatant will be transferred into a clean vial and capped to be stored at −20 °C until analysis.

##### Skeletal Muscle Biopsy

A rested muscle microbiopsy will be collected (Biofeather 14G needle with coaxial cannula [Medax]) from the *m. vastus lateralis* under local anesthetic. Muscle tissue will be immediately stored in dry ice and transferred to a −80 °C freezer for storage pending analysis.

##### Determination of Deuterium Body Water Enrichment

The protocol has been previously described [59,60]; brieﬂy, 100 μL of saliva will be heated in inverted 2-mL vials for 4 hours at 95 °C to purify fractions of body water. The vials will then be cooled on ice and the condensed body water transferred to a clean vial ready for injection on a high-temperature conversion elemental analyzer (Thermo Finnigan, Thermo Scientiﬁc) connected to an isotope ratio mass spectrometer (Delta V advantage, Thermo Scientiﬁc).

##### Determination of Protein-Bound Alanine Enrichment

To assess protein-bound alanine muscle fraction enrichment, approximately 30 mg of muscle will be homogenized in ice-cold homogenization buffer to isolate myoﬁbrillar proteins. After 10 minutes of mixing, samples will be centrifuged at 11,000 × g for 15 minutes at 4 °C. The supernatant (sarcoplasmic fraction) will be separated, and the pellet will be resuspended in 500 μL of mitochondrial extraction buffer. The pellet will then be homogenized using a Dounce homogenizer and centrifuged at 1000 × g for 5 minutes at 4 °C. Insoluble collagen will be separated following centrifugation from myoﬁbrillar proteins, which will be solubilized in 750 μL NaOH, precipitated using 1 M perchloric acid, and pelleted by centrifugation.

The plasma will be deproteinized using ice-cold ethanol (100%) and centrifuged at 17,000 × g for 10 minutes. The myofibrillar, collagen, and plasma pellets will be transferred to boiling tubes containing Dowex with 0.1 M HCl and hydrolyzed overnight at 110 °C for 16 to 20 hours. Following overnight hydrolysis, amino acids will be eluted with 2 M NH_4_OH and dried.

Dried samples will be resuspended in 60 μL of distilled water, 32 μL of methanol, 10 μL of pyridine, and 8 μL of methyl chloroformate with intermittent vortexing. The *n*-methoxycarbonyl methyl esters of the amino acids will then be extracted after adding 100 μL of chloroform. A molecular sieve will be added to remove water for approximately 20 seconds before being transferred to vials. Incorporation of deuterium into the protein-bound alanine will be determined by gas chromatography–pyrolysis–isotope ratio mass spectrometry (Delta V Advantage, Thermo).

##### Calculation of Fractional Synthetic Rate

The fractional synthetic rate (FSR) will be calculated using the incorporation of deuterium in alanine in myofibrillar, collagen, and plasma proteins (APE_Alanine_) and deuterium enrichment of body water from saliva, representing the precursor labeling between the blood sample and the muscle biopsy (APE_Precursor_), corrected for the mean number of deuterium moieties incorporated per alanine, 3.7, and the dilution from the total number of hydrogens in the derivative (ie, 11). The following calculation (Equation 1) will be used, where *t* represents the time between the baseline blood sample and the muscle biopsy:

##### Muscle Mass Analyses Using D3-Creatine

Whole-body muscle mass will be estimated using urinary D_3_-creatine at weeks 6, 12, 18, and 24 post partum (Figure 5). A single urine sample will be collected before ingestion of approximately 30 (SD 0.1) mg of D_3_-creatine tracer (D_3_-creatine, CK Isotopes) dissolved in approximately 50 mL of water. Participants will then collect all urine samples for 24 hours, starting immediately after tracer ingestion. A single urine sample will be collected 48 hours after tracer ingestion. The volume of urine collected over 24 hours will be recorded. Approximately 3 mL of each urine sample will be transferred to Eppendorf tubes and stored at −80 °C for later analysis.

**Figure 5 figure5:**
[figure not shown]
Procedures for muscle mass analyses using D_3_-creatine (D_3_Cr).

Urine will be thawed at room temperature. A standard curve using ^12^C- and ^13^C-creatine will be prepared for the determination of creatine concentration, and a D_3_-creatinine enrichment curve of 0% to 0.1% will be prepared. Once thawed, urine will be mixed, and 10 µL of ^13^C-creatine will be added to 50 µL of urine as an internal standard. A total of 250 µL of ice-cold acetonitrile will be added to samples and standards, vortex mixed, and left to incubate on ice for 30 minutes. Following incubation, samples will be centrifuged at 17,000 × g for 20 minutes. The supernatant will be transferred to vials ready for analysis using high-performance liquid chromatography–mass spectrometry.

From the measurement of urinary D_3_-creatinine enrichment it is possible to calculate total creatine pool size and, therefore, total muscle mass (Equation 2) [61], where *MW*_unlabeled_ and *MW*_labeled_ represent the molecular weights of both unlabeled and labeled creatine, respectively. The estimated creatine pool size will be divided by 4.3 g/kg, reflecting the concentration of creatine found in whole wet muscle mass.

##### Muscle Protein Breakdown Analyses Using D3-3-Methyl-Histidine

Muscle protein breakdown will be estimated using D_3_-3-methyl-histidine (D_3_-3MH) measured in urine at weeks 12 and 18 post partum (Figure 6). A single urine sample will be collected before ingestion of 10 mg of a methyl-D_3_-3MH tracer (D_3_-3MH, CK Isotopes) dissolved in 50 mL of water. Participants will void urine 18 hours after tracer ingestion before collecting spot samples at 20, 22, 24, and 26 hours after tracer ingestion. Approximately 3 mL of each urine sample will be stored in Eppendorf tubes at −80 °C until analysis.

A 0% to 10% D_3_-3MH enrichment curve will be prepared as a serial dilution and run alongside the samples. In total, 100 µL of urine will be aliquoted and deproteinized using 1 mL of MeCN:MeOH (1:1). Samples will be vortex mixed and incubated at −20 °C for 1 hour. Samples will be centrifuged at 17,000 × g for 5 minutes at 4 °C. The supernatant will be dried in the Techne Block at <40 °C using nitrogen gas, resuspended using 100 µL of acetonitrile: doubly deionized H_2_O (50:50), and analyzed using high-performance liquid chromatography–mass spectrometry.

The ratio of D_3_-3MH to 3-methyl-histidine will be determined, ratios will be corrected relative to the enrichment curve of each batch, and the atom percent excess will be determined. The predose, baseline urine sample will be used to correct for background enrichment and calculation of the atom percent excess. The ratios will be log-transformed and plotted against time to determine the decay rate.

**Figure 6 figure6:**
[figure not shown]
Procedures for muscle protein breakdown using D_3_-3-methyl-histidine (D_3_-3MH).

### Power Calculation

Kraemer et al [62] identified that single-lift strength was 39 (SD 7) kg and 37 (SD 5) kg for women at the end of a 6-month total strength and power and total strength and hypertrophy resistance training protocol, respectively, compared with 32 (SD 4) kg for women undertaking normal field-based military training. Based on the effect sizes between these training and control groups (total strength and power vs control, Cohen *d*=1.23; total strength and hypertrophy vs control, Cohen *d*=1.10), it is anticipated that between 9 and 11 women would be required per group to identify greater posttraining strength in the intervention group than in the control group, with a 1 − β of .80 and α of .05. Hendrickson et al [63] identified that squat and bench press 1 RM were 77 (SD 3) kg and 41 (SD 2) kg, respectively, for women at the end of a 12-week endurance and strength training program, compared with 68 (SD 4) kg and 34 (SD 2) kg for women in the control group, respectively. Based on the effect sizes between the training and control groups (squat, Cohen *d*=2.55; bench press, Cohen *d*=1.62), it is anticipated that between three and six women would be required per group to identify greater posttraining strength in the intervention group than in the control group, with a 1 − β of .80 and α of .05. Hendrickson et al [63], identified that a 3.2-km run time was 18.5 (SD 1.0) minutes for women at the end of a 12-week combined endurance and strength training program, compared with 22.1 (SD 1.2) minutes for women in the control group. Based on the effect sizes between the training and control groups (Cohen *d*=3.26), it is anticipated that 3 women would be required per group to identify greater aerobic fitness in the intervention group than in the control group, with a 1 − β of .80 and α of .05. As such, 11 participants per group would be sufficient to detect improved strength and aerobic fitness in the intervention group compared with the control group. To allow for dropout and noncompliance, we aim to recruit a minimum of 15 participants per group.

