### Statistical Analysis

To maximize statistical power, outcomes will be analyzed using mixed-effects linear models to leverage the collection of data on more than 2 time points and to facilitate the analysis of unbalanced data based on participant attrition. Participants will be included as random effects, with group and time included as fixed effects, to assess within- and between-group differences over time. Sensitivity analyses will be conducted by including baseline values in models or other data relative to potential confounders to account for nonrandom allocation. Linear models will be structured to assess within- and between-group differences over time (eg, the inclusion of resistance and HIIT exercise), establishing the rate of change of intervention and control and determining whether these rates are distinct. The suitability of the models will be established by assessing model residuals and transformations made if residuals are not normally distributed or homoscedastic. Uncertainty in parameter estimates will be quantified using the Satterthwaite approximation for *df* values or through bootstrapping procedures. To facilitate interpretation of the magnitude of change across different outcomes, analyses will be standardized relative to the baseline SD, thus placing outcomes on a unitless scale. Principal component analysis will be conducted on change scores to investigate the clustering of outcomes relative to the magnitude of change.

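### The sample-size counts reproduce only under a one-sided t test that is never declared; two-sided, 11 per group gives 69% power at the effect that sets the number. The bench press effect size does not follow from its own figures.

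*Protocol article*

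**What the plan says.** All the figures are in the Power Calculation section of the protocol article. Each count is given "with a 1 − β of .80 and α of .05", and sidedness is not mentioned. The strength counts are those needed "to identify greater posttraining strength in the intervention group than in the control group".

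- **Single-lift strength.** The training groups are described as "single-lift strength was 39 (SD 7) kg and 37 (SD 5) kg for women", against 32 (SD 4) kg in controls. The effect sizes are d=1.23 and "total strength and hypertrophy vs control, Cohen *d*=1.10". The conclusion is that "it is anticipated that between 9 and 11 women would be required per group".
- **Squat and bench press.** Squat is 77 (SD 3) against 68 (SD 4) kg, d=2.55. Bench press is 41 (SD 2) against 34 (SD 2) kg, with "bench press, Cohen *d*=1.62". The count is three to six per group.
- **3.2-km run.** 18.5 (SD 1.0) against 22.1 (SD 1.2) minutes, d=3.26, 3 per group.

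The section concludes that "11 participants per group would be sufficient to detect improved strength and aerobic fitness" and sets a recruitment minimum of 15 per group to cover dropout and noncompliance.

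The Statistical Analysis section plans mixed-effects linear models for differences within and between groups over time, with the aim of "establishing the rate of change of intervention and control and determining whether these rates are distinct". It names neither a one-sided nor a two-sided test.

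**The concern.** An α of .05 with no qualifier is normally read as two-sided. On that reading, four of the five stated counts are too small for 80% power, including both single-lift counts, and the larger of those (11) sets the sample size. The conclusion that 11 per group is enough then fails on its own inputs. The step from 11 to 15, offered as a margin for losses, is almost wholly used up by the number needed for analysis. That margin matters here: the Intervention Compliance section allows noncompliant participants to be excluded, and the Statistical Analysis section expects attrition.

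The bench press effect size is a separate matter. It is the only one of the five that cannot be recovered from the means and SDs printed beside it.

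**Working it through.** **Step 1. Effect sizes from the printed means and SDs.** Formula: d = difference in means / √((SD₁² + SD₂²)/2).

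| Comparison | Calculation | d | Stated d |
|---|---|---|---|
| Strength and power vs control | 7/√((49+16)/2) = 7/√32.5 | 1.228 | 1.23 |
| Strength and hypertrophy vs control | 5/√((25+16)/2) = 5/√20.5 | 1.104 | 1.10 |
| Squat | 9/√((9+16)/2) = 9/√12.5 | 2.546 | 2.55 |
| Bench press | 7/√((4+4)/2) = 7/2 | 3.50 | 1.62 |
| 3.2-km run | 3.6/√((1.44+1.00)/2) = 3.6/1.1045 | 3.259 | 3.26 |

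Four of the five agree, so the formula is the one the authors used. For bench press, d=1.62 would need a common SD of 7/1.62 = 4.3 kg, not 2 kg.

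**Step 2. Reproducing the stated counts.** The t-test columns use the exact noncentral t distribution with n per group, 2n − 2 degrees of freedom and noncentrality d√(n/2). Each entry is the smallest n per group with power of at least 80% at α=.05.

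| d as stated | Stated n | t, one-sided | t, two-sided | Normal, one-sided | Normal, two-sided |
|---|---|---|---|---|---|
| 1.23 | 9 | 9 (80.3%) | 12 (82.1%) | 9 | 11 |
| 1.10 | 11 | 11 (80.1%) | 15 (82.8%) | 11 | 13 |
| 2.55 | 3 | 3 (81.8%) | 4 (85.0%) | 2 | 3 |
| 1.62 | 6 | 6 (83.3%) | 8 (85.3%) | 5 | 6 |
| 3.26 | 3 | 3 (94.4%) | 3 (84.2%) | 2 | 2 |

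Only the one-sided t test matches all five.

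**Step 3. Power at the planned numbers (t test).**

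| n per group | d | One-sided .05 | Two-sided .05 |
|---|---|---|---|
| 11 | 1.10 | 80.1% | 69.0% |
| 11 | 1.23 | 87.3% | 78.3% |
| 14 | 1.10 | 88.3% | 79.99% |
| 15 | 1.10 | 90.2% | 82.8% |

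Two-sided, 11 per group reaches 80% power only for d of about 1.26, which is larger than either single-lift effect. For d=1.10 the two-sided requirement is 15 per group. With the unrounded d=1.104 it is 14 (80.3%). From a target of 15, that leaves 15 − 15 = 0 or 15 − 14 = 1 per group for losses.

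**Step 4. Bench press with the corrected effect size.** At d=3.50, 3 per group are enough (96.5% one-sided, 88.6% two-sided). The upper end of the stated three-to-six range therefore comes entirely from the 1.62. The 11 comes from single-lift strength and is unaffected.

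**The case against.** The strongest reply is that nothing was miscalculated. The Power Calculation section speaks of greater strength and greater aerobic fitness in the intervention group, and the Hypothesis section expects larger improvement there. A one-sided test fits that wording, and on it 11 per group gives the stated 80%. This stands in part: a reader might infer that the true power is 69% and the stated 80% simply false, and the documents do not support that. The 80% is right one-sided. But a directional hypothesis does not declare a one-sided test, no such test is declared in the article, and the description of the planned analysis leans non-directional without settling the matter. An unseen full protocol or analysis plan may fix the sidedness, yet the article prints the calculation and draws a sufficiency conclusion from it, so the label belongs there.

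Second, the 69% describes the simple post-training comparison used for sizing, not the planned mixed model. This also stands. If the model adjusted for the earlier measurement, two-sided power at 11 per group and d=1.10 would be about 73%, 81% or 93% for assumed correlations of .3, .5 or .7. The documents give no correlation, baseline values enter only as a sensitivity analysis, and an unadjusted change score gains nothing at a correlation of .5. The gain is possible but unquantified, so it cannot support the printed claim.

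Third, one might infer that 15 leaves no room at all for dropout. That is too strong. It depends on rounding d to 1.10, where 14 per group misses 80% by a hundredth of a point. With d=1.104 one per group remains; for d=1.23, 12 suffice and three remain. The 15 is also a minimum.

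Fourth, the bench press slip is conservative and has no design consequence. That is correct. Without the cited source it cannot be known whether the effect size or the means and SDs are misprinted.

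**Conclusion.** The point holds as a defect of statement. The sample-size justification depends on a one-sided α of .05 that it does not declare, and its sufficiency claim fails under the usual two-sided reading. At d=1.10, the effect that fixes the 11, power falls from 80% to 69%, about 11 percentage points. At d=1.23 it is 78%. The two-sided requirement for d=1.10 is 14 to 15 evaluable per group, so the margin for losses within 15 is at most about one per group at that effect. If all 15 per group are evaluable, two-sided power is 83%.

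These figures assume equal groups, the effect sizes taken from the cited studies and an unadjusted t test on post-training values. They do not give the power of the mixed model.

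The bench press effect size is inconsistent with its own inputs (3.50 against 1.62, 3 per group against 6). It should be corrected, but it does not alter the planned sample size.

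**What to change.** 1. State in the Power Calculation section that the counts use a one-sided α of .05, which is what the reproduction shows and the authors should confirm. Declare the sidedness of the primary between-group test.
2. If the primary test is two-sided, replace the claim that 11 per group is enough. Suggested wording: At a two-sided α of .05, a two-sample t test with 11 evaluable participants per group has 69% power for d=1.10 and reaches 80% only for d of about 1.26; with 15 evaluable per group, power for d=1.10 is 83%. If the primary test is one-sided, the 11 may stand with that label.
3. Correct the bench press effect size to 3.50 with 3 per group and revise the three-to-six range, or reconcile the printed means and SDs with the cited source.

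The cost is wording only. The fix requires no more participants, but on a two-sided reading the stated power becomes less favourable and the allowance for dropout is seen to be thin.
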